## 8.6 **Trial outcome measures**

### 8.6.1 Primary outcome measure

Primary outcome measure: Time from partial or complete remission (whichever documented first) to relapse of NS as defined below (Appendix 6):

- COMPLETE REMISSION (CR): PCR<50mg/mmol (only one result required).
- PARTIAL REMISSION (PR): Reduction in Urinary PCR  $\geq$  50% from Day 0 - Start of Protocolised Prednisolone Regimen (SPPR) AND PCR  $\geq$  50mg/mmol and  $\leq$  300mg/mmol on two consecutive results (performed within 14 days of each other). The date of first assessment is the date of partial remission.
- RELAPSE: recurrent NS as defined by albumin < 35 g/l, PCR > 300mg/mmol and an increase in 100% over the nadir value during remission on two consecutive results (performed within 14 days of each other). The date of first assessment is the date of relapse. For patients with an albumin  $\geq$  35g/l prior to relapse, only one PCR result is required (i.e. PCR > 300mg/mmol that has risen by 100% over the nadir value and an albumin < 35g/L).

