#### **11.5 Pre-remission trial visits – aligned with standard of care**

The following tests will be carried out every 4 (+/- 1 week) weeks until remission is achieved or until Week 16, whichever is earlier:

- Weight
- Blood pressure
- Haematology
- Biochemical analysis
- Urinary PCR
- 24 hour urine collection for proteinuria –week 16 only
- Concomitant medications - see section 10.3.3
- AE assessments

- Health status questionnaire: EQ-5D-5L
- Additional Health Costs questionnaire – week 16 only
- Prednisolone dosing
- CNI dosing (if applicable) at weeks 4, 8, 12, and 16

These procedures may be performed at a single visit, or may take place over a period of up to two weeks.

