#### 11.5.1 Week 16 Visit

Patients who have not responded to treatment by achieving partial or complete remission at the week 16 visit (16 weeks from Day 0, +/- 1 week) will leave the trial and return to standard of care treatment. These patients will not receive the third dose of rituximab or placebo at week 26 as they have not demonstrated steroid responsiveness, and on-going treatment with prednisolone with or without rituximab is likely to be futile.

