### 11.6 Remission Visit

The remission trial visit will:

- a. Be scheduled within two weeks of nephrotic symptoms resolving and urinalysis showing less +++ proteinuria on home or hospital testing
- b. Be taken to have occurred if blood and urine tests at a trial visit confirm remission

At the remission visit (or over a period of up to 2 weeks from resolution of nephrotic syndrome), procedures performed will be:

- Weight
- Blood pressure
- Haematology
- Biochemical analysis
- Urinary PCR
- 24 hour urine collection for proteinuria (within two weeks of remission visit)
- Concomitant medications - see section 10.3.3
- AE assessments
- Issue patients with urine dipsticks for monitoring
- Health status questionnaire: EQ-5D-5L
- Additional Health Costs questionnaire: out of pocket expenditure related to kidney, employment status, work productivity and activity impairment questionnaire, carer time
- Prednisolone dosing
- CNI dosing (if applicable)
- Immunoglobulins G and M

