#### 11.12 **Final trial visit**

The final trial visit will either be:

- At 16 weeks (+/- 1 week) from Day 0 (SPPR) for participants who have not entered complete or partial remission.
- At relapse (+ up to 2 week) for participants who have previously achieved complete or partial remission by week 16. Participants who have received placebo may then enter the Open Label Phase.
- Taken as the last 3 monthly visit they have had when the trial closes for participants who achieved complete or partial remission and did not relapse
- Please note: Trial participants withdrawn from treatment will require safety reporting (SAR/SUSAR only) for up to 12 months post last IMP dose providing that consent to participate in this trial is ongoing.

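### Partial remission needs two PCRs within 14 days, but no section schedules or requires the second, so some partial remitters may go unconfirmed and leave at week 16

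*Protocol*

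**What the plan says.** **Definition.** Section 8.6.1, repeated in 14.1 and Appendix 6, treats the two kinds of remission differently. For complete remission one sample is enough: "COMPLETE REMISSION (CR): PCR<50mg/mmol (only one result required". For partial remission the PCR must fall by at least half from Day 0 and lie between 50 and 300 mg/mmol "on two consecutive results (performed within 14 days of each other). The date of first assessment is the date of partial remission".

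**Schedule.** Section 11.5: "The following tests will be carried out every 4 (+/- 1 week) weeks until remission is achieved or until Week 16, whichever is earlier". It adds: "These procedures may be performed at a single visit, or may take place over a period of up to two weeks". Section 11.6 describes a remission visit with one urinary PCR. That visit is either arranged within two weeks of clinical and urinalysis improvement (a), or it will "Be taken to have occurred if blood and urine tests at a trial visit confirm remission" (b). Section 14.2 allows further tests when clinically indicated.

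**Exit.** Section 11.5.1: "Patients who have not responded to treatment by achieving partial or complete remission at the week 16 visit" (16 weeks from Day 0, one week either side) "will leave the trial and return to standard of care treatment". Section 11.12 places their final visit "At 16 weeks (+/- 1 week) from Day 0 (SPPR) for participants who have not entered complete or partial remission". The synopsis says that this withdrawal carries no further trial visits, and the week-16 footnote to table 11.15 repeats the withdrawal.

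**The concern.** The definition depends on a sample that the schedule does not provide. A patient can be in the partial-remission range at two successive scheduled visits and still not meet the definition. A site is then left to order an unscheduled repeat, to declare remission on one value contrary to 8.6.1, or to let the patient count as a non-responder.

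Remission status carries much of the trial:
- the time origin of the primary outcome (8.6.1);
- the responding population (16.1.1);
- the week-16 failure state in the probability-of-being-in-response model (16.1.2);
- the remission proportion, time to remission and time to treatment failure (8.6.2);
- eligibility for the third dose (10.1.7) and for the open-label phase (10.2);
- who leaves at week 16.

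The analysis plan cannot repair this, because it cannot supply a urine sample that was never taken.

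**Working it through.** **1. The plan's own figures.** These reproduce and are not in dispute.
- Events = 4(z₀.₉₇₅ + z_power)² / (ln HR)². With HR 0.50 and two-sided 5%, this gives 66, 75 and 88 events for 80%, 85% and 90% power. Section 16.2 and Appendix 5 state 67, 76 and 89.
- Event probability with 30 months' uniform accrual and 24 months' further follow-up = 1 − [exp(−24λ) − exp(−54λ)] / (30λ), where λ = ln 2 / median. Medians of 9 and 18 months give 0.939 and 0.765, mean 0.852. Then 78 × 0.852 = 66.4 events, against 67 stated.
- 112 × 0.70 = 78.4 remitters, as stated.

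**2. Gap between scheduled pre-remission PCRs.** Visits are anchored to Day 0, nominally 28 days apart, each with a window of ±7 days. If the earlier visit is shifted by a days and the later by b, the gap is 28 + b − a.
- Smallest gap: 28 − 7 − 7 = 14 days. Largest: 28 + 7 + 7 = 42 days.
- There are 15 × 15 = 225 combinations of a and b. Only one (a = +7, b = −7) gives 14 days or less: 1/225 = 0.4%, if days are spread evenly over the windows.

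**3. If the first in-range visit is itself taken as the remission visit under 11.6(b).** The next scheduled PCR is the first post-remission visit (11.7), at 28 ± 7 = 21 to 35 days. That is always outside the 14-day limit.

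**4. Other routes to a second PCR.**

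| Route | Can it supply the second PCR? | Does it require it? |
|---|---|---|
| Remission visit, 11.6(a) | Yes, if an in-range PCR came shortly before | No. The trigger is symptoms and urinalysis, so this visit may give the first value; only one PCR is listed |
| Remission visit, 11.6(b) | No, it is the same visit | No. It can be read as letting one visit suffice |
| Two-week spread of procedures, 11.5 and 11.14 | Yes, if a site uses it for a repeat | No. It spreads one visit's tests |
| Extra tests, 14.2 | Yes | No, discretionary |

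Home dipsticks do not help. They are first issued at the remission visit, and under 11.11 patients in partial remission do not self-test.

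**5. First in-range value at week 16.** The visit may fall up to day 17 × 7 = 119, so a valid repeat could fall as late as day 119 + 14 = 133 (week 19). Because remission is dated to the first result, such a repeat would still give remission dated to the week-16 visit. But for a patient not yet confirmed in remission, 11.12 makes week 16 the final visit and no later PCR is scheduled.

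**6. Relapse.** The same two-in-14-days rule applies unless albumin was at least 35 g/l beforehand, when one PCR is enough. If a scheduled PCR raises the alarm, the relapse visit within two weeks (11.11) gives the second result. The gap remains only where symptoms or a dipstick prompt the visit, so that it gives the first qualifying PCR, and prior albumin was below 35 g/l.

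**The case against.** The strongest reply is that the definition itself demands the second result, so a competent site will obtain it, and the protocol leaves room to do so: the remission visit, the two-week visit spread and the extra tests in 14.2. The exit in 11.12 covers only patients who have not entered remission, and dating to the first result means that a prompt repeat after week 16 still counts. Patients who go on to complete remission need one sample. RaDaR data uploaded at trial end (11.2.1) may capture local repeats. All of this stands, and it limits the point to possible rather than certain loss. It does not close the gap, because no route is compulsory and RaDaR cannot capture a test that was not done.

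Some stronger readings are tempting, but the documents do not support them:
- **Partial remitters will certainly be removed, or a week-16 value cannot be confirmed.** The routes above make confirmation possible.
- **Power falls by a stated amount.** A reader might take the share of partial remissions from the cited series of 41 adults (section 6.2.3): 7 of 25 + 7 = 32, or 22%. Those were rituximab-treated patients with steroid-dependent or frequently relapsing minimal change disease. This trial includes FSGS and de novo disease, and half the patients receive placebo. The documents give no repeat-testing rate either. Section 16.5 also holds the trial open until at least 76 events.
- **Relapse is affected in general.** It is affected only in the narrow case in step 6.
- **The next scheduled PCR could simply serve as confirmation.** Permitted gaps reach 42 days, the prednisolone reduction starts at most two weeks after remission (10.3.1), so a late sample could fall within the taper, and relapse visits later become 3-monthly.

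**Conclusion.** The concern holds as a mismatch between endpoint definition and schedule. Routine visits alone almost never confirm partial remission, no section requires the confirming sample, and a value first in range at week 16 has no scheduled confirmation. Whether a partial remitter is recorded as a responder or as a treatment failure therefore depends in part on local testing practice.

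The number affected cannot be derived. It depends on the share of partial remissions, how many are first seen at week 16, how many later reach complete remission and how often sites repeat the test; the protocol gives none of these for its own population. The 0.4% in step 2 describes the timetable only and assumes evenly spread visit days; it is not a rate of missed remissions. Because of the 76-event minimum, any loss of remitters may appear as longer follow-up rather than lower power. Responders misclassified as failures would remain either way.

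**What to change.** - Keep the 14-day definition. Add a required repeat spot PCR within 14 days of a first qualifying value to sections 11.5, 11.6 and 11.11 and to table 11.15, including after a first partial-range value at the week-16 visit.
- For the endpoint, keep dating remission to the first result once the repeat confirms it.
- Reconcile 11.6(b), 11.5.1, 11.12, the synopsis withdrawal criterion and the week-16 footnote to table 11.15 with the definition in 8.6.1, 14.1 and Appendix 6. How patients are managed while a repeat is pending is a clinical matter for the trial team, and nothing is proposed on it here.

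The cost is protocol wording and one extra spot urine in patients with a first partial-range value (and in the narrow relapse case), which the definition already implies. The sample-size section needs no change. The change helps only patients assessed after it takes effect, because a sample not taken within 14 days cannot be recovered later.

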### 8.6.2 Secondary outcome measures

Secondary assessments will include an evaluation of the effect of rituximab on:

- Proportion of patients achieving partial or complete remission
- Time to partial or complete remission from Day 0 (SPPR)
- Time to treatment failure (not achieving remission by week 16 or relapse) from randomisation
- Serious AEs
- AE of Special Interest, including infection and steroid-associated side effects
- Change in urinary PCR/24 hour proteinuria
- Change in serum albumin
- Kidney function as assessed by the change in Glomerular filtration rate (GFR) from Day 0 - Start of Protocolised Prednisolone Regimen (SPPR) to 24 months and to trial end
- Health Status (EQ-5D-5L)
- NHS resource use, out of pocket expenditure and morbidity-related lost productivity, (Additional Health Costs)

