### 8.5.2 Secondary objectives

- Assess the effect of rituximab on NHS and societal resource use and hence cost.
- Assess the effect of rituximab on safety and on secondary measures of efficacy, such as achievement of partial and complete remission of NS and the preservation of renal function.
- Assess the effect of rituximab on health status of participant.

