## 9 SELECTION AND WITHDRAWAL OF PARTICIPANTS

### 9.1 Inclusion criteria

To be included in the trial the participant must:

- Have given written informed consent to participate
- Age 16 years or older at the time of consent
- Have confirmed NS at Day 0 (Start of Protocolised Prednisolone regimen (SPPR)) (defined as serum albumin < 35g/l and PCR>300mg/mmol) secondary to MCD/FSGS with,
  - *De novo* disease, or;
  - Relapsing disease in a patient previously steroid or CNI responsive (this is defined as patients who have achieved complete or partial remission from their NS in response to treatment with steroid or CNI).
- Biopsy proven MCD or FSGS (from medical records)
- Agreed to be enrolled in the National Registry of Rare Renal Diseases (RaDaR)

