##### 9.5.1 *Withdrawal from protocol treatment*

A participant may withdraw, or be withdrawn, from the trial treatment for the following reasons:

- Participants who do not achieve partial remission by 16 weeks after Day 0 (SPPR). The treating clinician may request unblinding of withdrawn participants if required for safety consideration of future treatment – this unblinding will be performed at local site level only
- Participants who enter the trial and remit and relapse before receiving the first dose of trial IMP. In this case the participant can be withdrawn from the trial and re-screened as a new participant. It is recommended the clinician chooses Regimen 1 steroid taper for this participant when re-entering them into the trial
- Progressed or relapsed disease whilst on therapy
- Unacceptable toxicity
- Participant choice
- Addition of other immunosuppressants for treatment of MCD/FSGS
- Any alterations in the participant's condition which justifies the discontinuation of treatment in the investigator's opinion.
- Failure to adhere to infusion visit schedule. With ongoing consent, patients should remain in the trial and be followed up according to the protocol visit schedules. Samples and data collected up to the time of withdrawal will be included in the data reported for the trial.

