### 11.3 Screening Evaluation

#### *11.3.1 Screening and Day 0*

Screening and Day 0 (SPPR) visits may be performed separately, within a period of four weeks, or in a single combined visit wherever possible. Patients will start treatment with the pre-specified prednisolone regime (see Section 10.3) at the Day 0 (SPPR) visit, which may occur simultaneously with the screening visit if the treating clinician considers this clinically appropriate according to usual care. This may be before all data are available to determine eligibility.

Patients who have started Standard of Care treatment with prednisolone prior to consent may be enrolled in the trial if:

- the prednisolone was started within 4 weeks,
- the dosing used is consistent with the SPPR (section 10.3.1),
- patients are randomised and receive IMP within 4 weeks of starting SPPR.

In this situation, Day 0 would be when they started treatment with prednisolone for new onset/relapse of nephrotic syndrome. For these patients, serum albumin and urinary PCR tests will have been performed within the 7 days preceding SPPR (i.e. Day 0 -7). Patients may have been receiving more than 60mg prednisolone daily prior to randomisation. These patients are still eligible for the trial (if they have been receiving this dose for less than 4 weeks). In this group of patients, the prednisolone will be reduced to 60mg within 48 hours of randomisation.

Eligible participants will subsequently be randomised by a suitably trained and delegated member of the research team as described in Section 9.3 and the trial manual.

Trial visits, including screening and Day 0 assessments will be performed at the outpatient clinics.

Trial specific assessments will only be conducted after participants have given written informed consent. Where possible, eligibility blood and urine results will be obtained from standard of care visits.

Participants will be provided a container to collect 24 hour urine sample which they may bring back to the clinic during their next visit (< 4 weeks from Day 0). It is recommended that participants collect all urine produced starting from second urine of any day up until first urine of the following day.

Screening and Day 0 (SPPR) visits (which may be combined or occur over a period of up to 4 weeks) will include the following assessments:

- Demographics information
- Relevant medical history
- Height and weight

- Blood pressure
- Haematology
- Biochemical analysis

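### Timing remission from the start of prednisolone counts remissions already present at randomisation, which dilutes the remission comparison without biasing it

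*Protocol*

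**What the plan says.** Section 8.5.2 makes remission part of a secondary objective, naming "secondary measures of efficacy, such as achievement of partial and complete remission of NS and the preservation of renal function". Section 8.6.2 serves it with two outcomes: "Proportion of patients achieving partial or complete remission", with no restriction on when the remission began, and "Time to partial or complete remission from Day 0 (SPPR" (the start of protocolised prednisolone). A third item in the same list uses another origin: "Time to treatment failure (not achieving remission by week 16 or relapse) from randomisation".

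Eligibility in 9.1 asks participants to "Have confirmed NS at Day 0". Neither 9.1 nor 9.2 asks for a further check of nephrotic state at randomisation. Section 11.3.1 admits patients who began prednisolone before consent, provided that "patients are randomised and receive IMP within 4 weeks of starting SPPR"; for them "Day 0 would be when they started treatment with prednisolone for new onset/relapse of nephrotic syndrome".

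Section 9.5.1 provides for "Participants who enter the trial and remit and relapse before receiving the first dose of trial IMP", who can be withdrawn and re-screened. It makes no provision for someone who remits before the first dose and stays in remission.

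**The concern.** A participant can be nephrotic at Day 0, respond to prednisolone, and be in remission when randomised. That remission is a fact about the participant before allocation, yet 8.6.2 counts it as an outcome. Across the two arms such events have an expected hazard ratio of 1, so they water down whatever effect rituximab has on later remissions.

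Early remission is plausible on the protocol's own account. Section 6.2.1 says MCD responds faster than FSGS and gives a 90% response rate. Section 10.3.1 offers Regimen 2 to people who responded quickly before. One PCR below 50 mg/mmol is enough for complete remission (8.6.1). The first scheduled remission assessment is week 4 plus or minus 1 (14.2), which can fall before a week-4 first dose.

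Two things are at stake. The remission objective could look negative partly because of where the clock starts. Also, section 16.1.2 (read as a condition, since the alternative follows it) uses the log-rank test when time to remission does not differ between arms and the PBRF otherwise. Dilution makes a real difference harder to see at that step.

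**Working it through.** **The plan's own figure.** For the primary outcome, events = 4(1.960 + 0.842)² / (ln 0.5)² = 65.3, so 66 against the stated 67. With exponential medians of 9 and 18 months, 30 months of accrual and 24 more of follow-up, the event probabilities are 0.939 and 0.765, mean 0.852. Then 66 / 0.852 = 77.5, so 78 as stated. This sample size is reproduced and is not affected by the point made here. The protocol states no power for remission, so the rest is illustration.

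**Inputs.** From the protocol: N = 130 (the lower planned total, 16.2), 1:1 allocation (8.1), 75% remission (16.2) and the week-16 limit (11.5.1). Assumed: 75% remitted by week 16 in the control arm at constant hazard from Day 0, hence a median of 8 weeks; a remission hazard ratio of 2.0 acting only after dose 1; and, at first, randomisation and dose 1 on the same day, week t.

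**Formulas.**
- Share remitted before week t: s = 1 − 2^(−t/8).
- Remitted by week 16 on rituximab: 1 − (1 − s) × 2^(−2(16 − t)/8).
- E = 130 × the mean of the two arms' proportions; early fraction f = 130s / E.
- Apparent Day 0 log hazard ratio ≈ (1 − f) × ln 2.
- Power = Φ(log hazard ratio × √(events/4) − 1.96).
- From randomisation, among those not yet in remission: E − 130s events at the full ratio of 2.0.

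| t (weeks) | s | E | f | Day 0 hazard ratio | Day 0 power | Events from randomisation | Power from randomisation |
|---|---|---|---|---|---|---|---|
| 0 | 0 | 109.7 | 0 | 2.00 | 95% | 109.7 | 95% |
| 2 | 0.159 | 108.9 | 0.190 | 1.75 | 83% | 88.2 | 90% |
| 3 | 0.229 | 108.5 | 0.274 | 1.65 | 74% | 78.7 | 87% |
| 4 | 0.293 | 108.0 | 0.353 | 1.57 | 64% | 69.9 | 83% |

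A simulation of 60,000 participants with Cox estimates agrees: 1.77, 1.65 and 1.54 at weeks 2, 3 and 4, with power 84, 74 and 61% from Day 0 against 91, 87 and 80%. The gaps are about 7, 12–13 and 18–19 points.

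**Randomisation before dose 1.** Take randomisation at week 2 and dose 1 at week 4. The restriction removes only 130 × 0.159 = 20.7 events and leaves 108.0 − 20.7 = 87.3. Of these, 38.1 − 20.7 = 17.4 (a fraction of 0.199) still precede dose 1. The log ratio is 0.801 × 0.693 = 0.555, and power is Φ(0.555 × √21.8 − 1.96) = 74%, against 64% from Day 0: a gap of 9 points before rounding. For weeks 1 and 3 the same steps give 79% against 74%, about 4 points.

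**Slower early remission.** Assume no documented remission before week 2 and 75% by week 16, so the hazard is ln 4 / 14 per week from week 2. With randomisation and dose together at week 2, 3 or 4, s is 0, 0.094 and 0.180, and the gaps are 0, 3 and 8 points. With none before week 3, the gap at week 4 is 3 to 4 points.

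**Smaller effect.** With a true ratio of 1.5 and constant hazard from Day 0, power is about 38, 32 and 26% from Day 0 (weeks 2, 3, 4) and about 46, 42 and 38% from randomisation.

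**Proportion remitting.** Suppose 20% of all participants have remitted by randomisation. Over all randomised the comparison is 75% against 92.2% (17.2 points, power 76%). Among the rest it is (0.75 − 0.20)/0.80 = 68.8% against 1 − 0.3125² = 90.2% (21.5 points, 52 per arm, power 78%). Here the restriction sharpens the estimate more than it raises power.

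**The case against.** The strongest reply is that Day 0 is the protocol's common clock. Partial remission is measured against the Day 0 PCR, and visits, the week-16 limit and GFR change all run from Day 0. An origin shared by both arms gives a valid intention-to-treat comparison. This stands: the choice is defensible and contradicts nothing. A reader might infer a contradiction from the randomisation origin of time to treatment failure, but that is a different composite and may have its own origin.

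The second reply concerns size. Remissions between randomisation and dose 1 are legitimate outcomes and no change of clock removes them, so calculations that put both on the same day show the largest possible recovery. A constant hazard from Day 0 also places many remissions before any scheduled assessment, and partial remission needs two results. Both criticisms stand and are why a range is given. The hazard ratio of 2.0 has no source in the protocol, and at 1.5 the outcome is underpowered on either clock.

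A reader might take 9.5.1 as evidence that remission before the first dose is common. It shows only that the possibility was foreseen.

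Third, no PCR is scheduled at randomisation (11.15), so status there is often unknown. This limits the fix but does not defeat it, provided that the rule uses documented status only. Nor can the matter be left wholly to an analysis plan, because 8.6.2 itself fixes the Day 0 origin.

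**Conclusion.** The point holds as a loss of contrast and power in the remission outcomes. Under a hazard ratio of 2.0 and N = 130, the loss lies between 0 and just under 20 points. It is about 4 to 9 points if randomisation comes two weeks before dose 1 (at weeks 1 or 2), and 0 to about 8 if nobody is documented in remission before week 2. The upper end needs constant hazard from Day 0 with randomisation and dose 1 both at week 4. It should not be read as the expected loss, because the protocol gives no share remitting before randomisation.

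Two stronger readings are tempting and unsupported. One is that the Day 0 clock biases the trial or creates false positives: randomisation balances the early remissions, so they only move the estimate toward no difference. The other is that the primary outcome is seriously affected. A remission dated before randomisation does bring relapse-free time that predates allocation, but that is at most 4 weeks, balanced between arms, against planning medians of 9 and 18 months.

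The change is worth making because it is cheap and concerns a stated objective.

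**What to change.** In 8.6.2, count participants as at risk for remission from randomisation, either by timing from randomisation or by keeping the Day 0 clock with entry at randomisation. Report the proportion remitting in the same set: participants with no remission documented from results available on or before the randomisation date. This is a baseline status, so the randomised comparison stays valid. Nobody should be excluded because of a confirmatory result obtained after randomisation. Since partial remission is dated to the first of its two results, the text should also say what date such a remission carries, by one rule for both arms.

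Keep the all-randomised Day 0 analysis alongside, and let 16.1.2 say which of the two it means by time to remission.

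The cost is wording plus recording status at randomisation from results already held; no visit or treatment changes. The downside is that participants already in documented remission leave the main remission comparison, and that status is known only where a result exists. For the primary outcome, delayed entry at randomisation for remissions dated earlier is an optional, minor refinement.
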